### **11.2.1 Protocol Adherence**

This protocol defines the study objectives, the study procedures and the data to be collected about study patients. Additional assessments required to ensure safety of patients should be performed as deemed necessary on a case-by-case basis. Under no circumstances is an Investigator allowed to collect additional data or conduct any additional procedures for any research-related purpose involving any investigational drugs under this protocol.

Investigators agree to be diligent in avoiding protocol deviations. If an Investigator feels a protocol deviation would improve the conduct of the study, this deviation must be considered as a protocol amendment. Unless such an amendment is agreed upon by the Sponsor and approved by the IRB/IEC and health authorities, where required, it cannot be implemented unless necessary to eliminate immediate hazard to the patient.

### **11.2.2 Protocol Modification and Amendments**

No modifications to the protocol should be made without prior approval of the IRB/IEC.

When circumstances require an urgent departure from procedures defined in the protocol, the Investigator will contact the Sponsor to discuss the planned course of action. Any departures from the protocol must be fully documented in the source documentation and in the protocol deviation log.

Any protocol amendments will be prepared by the Sponsor. Protocol amendments will be submitted to the IRB/IEC and to regulatory authorities where required by and in accordance with EU and local regulatory requirements. Where approval by the IRB/IEC and/or regulatory authorities is required, the changes will not be implemented until this approval is received, except where the change is required as an urgent safety measure as defined by ICH guidelines.

### **11.2.3 Coordinating Investigator**

If a Coordinating Investigator is assigned for the clinical study, they will be designated by mutual agreement.

## **11.3 Study Termination**

The Sponsor will terminate this study following completion of the study objectives or earlier if deemed necessary.

The Sponsor reserves the right to terminate the study or dosing schedules thereof at any time. If the Sponsor becomes aware of information on matters concerning the quality, efficacy or safety of the study treatment or any other study treatment information that may affect proper conduct of the clinical study, the Sponsor may terminate the study. The Sponsor will send a written notice of the termination along with the reasons to the competent authorities, the IEC/IRB and the Investigators. If an Investigator or the Investigator's IEC/IRB intends to terminate participation in the study, the Investigator must immediately inform the Sponsor and provide the reason for it.

## **11.4 Site Discontinuation**

The Sponsor has the right to close a site at any time. Reasons for closing a site may include but are not limited to:

- Excessively slow recruitment
- Poor protocol adherence
- Inaccurate or incomplete data recording
- Non-compliance with the ICH guideline for GCP
- No study activity (i.e. all patients have completed and all obligations have been fulfilled)

## **11.5 Publication of Study Protocol and Results**

The results of this study may be published and/or presented at scientific meetings. The Sponsor encourages publication of clinical study data in reputable peer reviewed journals. Authorship will be discussed and agreed in advance in accordance with standard editorial and ethical practice. Prior to publication, the Sponsor will review and comment before its submission to the journal. In cases where the Sponsor considers that the proposed publication contains patentable material or information which should be protected as valuable confidential information, the Sponsor reserves the right to delay submission to the journal until patent applications have been filed and/or require the deletion of the confidential information from the proposed publication.

Authorship will be determined by mutual agreement and in line with International Committee of Medical Journal Editors (ICMJE) authorship guidelines.

## **11.6 Dissemination of Clinical Study Data**

Dissemination of the results of this study will be in accordance with current regulatory guidance.

## **11.7 Audits and Inspections**

The Sponsor may conduct audits of clinical study activities in accordance with internal standard operating procedures to evaluate compliance with the principles of GCP and ICH related guidelines.

A regulatory authority may also wish to conduct an inspection (during the study or after its completion). Should regulatory authorities request an inspection, the Investigator must inform the Sponsor or designee immediately that such request has been made.

## **11.8 Liability, Insurance and Financial Disclosures**

Liability and insurance provisions for this study are provided separately. The Sponsor has taken out an insurance covering their civil responsibility. A copy of the country-specific insurance certificates will be maintained in the Investigator File and Trial Master File. Details of the insurance will be made available to patients in the ICF.

Investigators and Sub-Investigators will provide the Sponsor with sufficient, accurate financial information in accordance with local regulations to allow the Sponsor to submit complete and accurate financial certification or disclosure statements to the appropriate regulatory authorities.

## 12 APPENDICES

### 12.1 Appendix: ECOG Performance Status

| Grade | ECOG Performance Status                                                                                                                                  |
|-------|----------------------------------------------------------------------------------------------------------------------------------------------------------|
| 0     | Fully active, able to carry on all pre-disease performance without restriction                                                                           |
| 1     | Restricted in physically strenuous activity but ambulatory and able to carry out work of a light or sedentary nature, e.g. light house work, office work |
| 2     | Ambulatory and capable of all self-care but unable to carry out any work activities. Up and about more than 50% of waking hours.                         |
| 3     | Capable of only limited self-care, confined to bed or chair more than 50% of waking hours                                                                |
| 4     | Completely disabled. Cannot carry on any self-care. Totally confined to bed or chair.                                                                    |
| 5     | Dead                                                                                                                                                     |

ECOG, Eastern Cooperative Oncology Group.

Source: Oken

CONFIDENTIAL

May not be used, divulged, published, or otherwise disclosed without the consent of  
Molecular Partners AG, Schlieren, Switzerland

## 12.2 Appendix: Contraceptive Guidance

### Females of Childbearing Potential (FCBP)

A female is considered fertile following menarche and until becoming postmenopausal unless permanently sterile. Permanent sterilization methods include hysterectomy, bilateral salpingectomy and bilateral oophorectomy.

Females in the following categories are not considered FCBP:

1. Premenopausal female with one of the following:

- a. Documented hysterectomy
- b. Documented bilateral salpingectomy
- c. Documented bilateral oophorectomy

Note: Documentation can come from the site personnel by review of patient medical records, physical examination or medical history interview.

2. Postmenopausal female:

- a. A postmenopausal state is defined as no menses for 12 months without an alternative medical cause. A high follicle stimulating hormone (FSH) level in the postmenopausal range may be used to confirm a postmenopausal state in females not using hormonal contraception or hormonal replacement therapy (HRT). However, in the absence of 12 months of amenorrhea, a single FSH measurement is insufficient.
- b. Females on HRT and whose menopausal status is in doubt will be required to use one of the non-hormonal highly effective contraception methods if they wish to continue their HRT during the study. Otherwise, they must discontinue HRT to allow confirmation of postmenopausal status before study enrollment.

### Contraception Guidance

#### Female Patients

**Highly effective contraceptive methods that are user dependent** (*failure rate of < 1% per year when used consistently and correctlya*)

- Combined (estrogen and progestin-containing) hormonal contraception associated with inhibition of ovulationb
  - Oral
  - Intravaginal
  - Transdermal
- Progestin-only hormonal contraception associated with inhibition of ovulationb
  - Oral
  - Injectable

**Highly effective methods that are user independent** (*failure rate of < 1% per year*)

- Implantable progestin-only hormonal contraception associated with inhibition of ovulationb
- Intrauterine device
- Intrauterine hormone-releasing system
- Bilateral tubal occlusion

- Vasectomized partner: If the partner is the sole male sexual partner of the FCBP and the absence of sperm has been confirmed. If not, an additional highly effective method of contraception should be used.
- Sexual abstinence: Defined as refraining from heterosexual intercourse during the treatment period and for at least 3 months after last dose of study treatment. The reliability of sexual abstinence needs to be evaluated in relation to the duration of the study and the preferred and usual lifestyle of the patient.

Periodic abstinence (e.g. calendar, ovulation, symptothermal or postovulation methods) and withdrawal are **not** acceptable methods of contraception

a Typical use failure rates may differ from those when used consistently and correctly. Use should be consistent with local regulations regarding the use of contraceptive methods for patients participating in clinical studies.

b Hormonal contraception may be susceptible to interaction with certain concomitant medications, which may reduce the efficacy of the contraceptive method. In this case, 2 highly effective methods of contraception may be considered during the treatment period and for at least 3 months after the last study drug administration.

### **Male Patients**

Male patients with female partners of childbearing potential are eligible to participate in the study if the following criteria apply throughout the study and for 3 months after the last study drug administration:

- Are abstinent from penile-vaginal intercourse as their usual and preferred lifestyle (abstinent on a long-term and persistent basis) and agree to remain abstinent for duration of study and for at least 3 months after the last dose of the study treatment.
- Female partner is using a highly effective contraceptive method.
- Agree to use a male condom plus an additional method with a failure rate of < 1% per year as described above when having penile-vaginal intercourse with a FCBP.
- Men with a pregnant or breastfeeding partner must agree to remain abstinent from penile-vaginal intercourse or use a male condom during each episode of penile penetration during the study.
- Refrain from donating sperm for the duration of the study and for at least 3 months after the last dose of the study treatment.

## 12.3 Appendix: Response Evaluation with RECIST v1.1

**Table 25. RECIST v1.1 Guidelines for Tumor Response**

| Disease Response Criteria for Target and Non-target Lesions |                                                                                                                                                                                                                                                                                                           |
|-------------------------------------------------------------|-----------------------------------------------------------------------------------------------------------------------------------------------------------------------------------------------------------------------------------------------------------------------------------------------------------|
| Evaluation of Target Lesions                                |                                                                                                                                                                                                                                                                                                           |
| Complete Response (CR)                                      | Disappearance of all target lesions. Pathologic nodes must have a reduction in the short axis to < 10 mm.                                                                                                                                                                                                 |
| Partial Response (PR)                                       | At least a 30% decrease in the sum of the diameters of target lesions, taking as reference the baseline sum diameters.                                                                                                                                                                                    |
| Stable Disease (SD)                                         | Neither sufficient shrinkage to qualify for PR nor sufficient increase to qualify for PD, taking as reference the smallest sum LD since the treatment started.                                                                                                                                            |
| Progressive Disease (PD)                                    | At least a 20% increase in the sum of the diameters of target lesions, taking as reference the smallest sum on study recorded since the treatment started or the appearance of one or more new lesions. In addition to 20% increase, the sum must also demonstrate an absolute increase of at least 5 mm. |
| Evaluation of Non-target Lesions                            |                                                                                                                                                                                                                                                                                                           |
| Complete Response (CR)                                      | Disappearance of all non-target lesions and normalization of tumor marker level.                                                                                                                                                                                                                          |
| Incomplete Response/Stable Disease (SD)                     | Persistence of one or more non-target lesion(s) or/and maintenance of tumor marker level above the normal limits.                                                                                                                                                                                         |
| Progressive Disease (PD)                                    | Appearance of one or more new lesions and/or unequivocal progression of existing non-target lesions.                                                                                                                                                                                                      |

CR, complete response; LD, longest diameter; PD, progressive disease; PR, partial response; SD, stable disease.

**Table 26. RECIST v1.1 Overall Response Criteria**

| Patients with Target and Non-target Lesions |                             |             |                  |
|---------------------------------------------|-----------------------------|-------------|------------------|
| Target Lesions                              | Non-Target Lesions          | New Lesions | Overall Response |
| CR                                          | CR                          | No          | CR               |
| CR                                          | Non-CR/Non-PD               | No          | PR               |
| CR                                          | Not evaluated               | No          | PR               |
| PR                                          | Non-PD or not all evaluated | No          | PR               |
| SD                                          | Non-PD or not all evaluated | No          | SD               |
| Not evaluated                               | Non-PD                      | No          | NE               |
| PD                                          | Any                         | Yes or no   | PD               |
| Any                                         | PD                          | Yes or no   | PD               |
| Any                                         | Any                         | Yes         | PD               |
| Patients with Non-target Lesions Only       |                             |             |                  |
| Non-Target Lesions                          | New Lesions                 |             | Overall Response |
| CR                                          | No                          |             | CR               |
| Non-CR/Non-PD                               | No                          |             | Non-CR/Non-PD    |
| Not all evaluated                           | No                          |             | NE               |
| Unequivocal PD                              | Yes or No                   |             | PD               |
| Any                                         | Yes                         |             | PD               |

CR, complete response; NE, not evaluable; PD, progressive disease; PR, partial response; SD, stable disease.

Source: Eisenhauer

## 12.4 Appendix: Evaluation and Guidance Using iRECIST

After RECIST v1.1 defined progressive disease (PD) is identified at any time point, a patient may continue treatment if clinically stable, at the discretion of the Investigator. Obtain repeat imaging 4 to 8 weeks later to confirm PD. If PD is not confirmed, treatment can continue.

If PD is confirmed and the patient is still deriving a clinical benefit, contact the Sponsor to discuss continuing treatment, and if granted, document the Sponsor approval to continue to treat beyond confirmed PD per protocol. At this first PD visit, enter both RECIST v1.1 response and iRECIST response. At all following visits, enter iRECIST response data only.

For visits after the visit when radiographic PD is first seen, complete the eCRF for treatment beyond radiographic progression.

Once immune confirmed PD (iCPD) occurs, treatment should generally be discontinued.

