## **7.3 Treatment Period and Follow-up**

### **7.3.1 Treatment Period and End of Treatment**

On-study evaluations will be performed as per the schedule of assessments (Section 7.1) and as detailed in Section 7.4. Assessments during unscheduled visits should be performed as clinically indicated and recorded in the eCRF.

Laboratory assessments performed as a part of the screening evaluations within 48 hours before the first study drug administration are not required to be repeated on the day of first study drug administration (Section 5.2.3).

Allowed visit/assessment windows are detailed in Table 8 to Table 13 (q3w dosing schedule) and Table 15 to Table 20 (q1w dosing schedule), and will not constitute a protocol deviation.

Patients can only receive study treatment if the requirements specified in Sections 5.2.3 and 5.2.9 are met.

Study treatment will be administered as described in Section 5.2.2 until any of the events described in Section 7.3.4 occurs (EOT). The EOT date is defined as the date when the decision is taken for the patient to discontinue from study treatment for any reason.

Treatment beyond PD will be allowed as per iRECIST if the Investigator believes that the patient is still receiving clinical benefit from study treatment and that the potential benefit of continuing study treatment outweighs any potential risk, and only with Sponsor approval.

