### 7.3.4 Patient Discontinuation

The reason(s) for discontinuation and the corresponding dates must be documented in the patient's source documents and in the eCRF.

A patient will be discontinued from study treatment (EOT) and/or the study (EOS) for any of the following reasons:

- PD
- Unacceptable toxicity
- Patient refusal to continue study treatment a
- Withdrawal of consent
- Pregnancy (Section 8.3)
- Study terminated by Sponsor
- Lost to follow-up b
- Death
- Investigator decision
- Screen failure
- Other

a Patients who wish to discontinue from further study treatment should be encouraged to complete the safety and/or survival FU.

b Patients will be considered lost to follow-up if they miss 3 consecutive study contacts by clinic visits and/or telephone.

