#### **7.4.15 Efficacy Assessments**

Patients will be evaluated for response using RECIST v1.1 (Appendix 12.3) and iRECIST (Appendix 12.4) as per Investigator assessment.

Tumor measurements will be made at screening and every 6 to 8 weeks after the start of study treatment (within 7 days before scheduled infusion on Day 1 of Cycles 3, 5 and 8 then every third cycle and according to institutional standard practice) until PD, withdrawal of consent, death, or study termination, whichever occurs first. Tumor assessment results must be available before next planned study drug administration that follows the tumor assessment.

CT scans will be performed using institutional standard operating procedures. In specific cases, tumor measurements may be performed by magnetic resonance imaging (MRI) scans instead of (or in addition to) CT scans. However, the same imaging modality as used for screening should be used throughout the study. Scans will be read by institutional radiologists and reported. The reports will be filed in source documents and the results entered into the eCRF.

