**Table 27. iRECIST Response Criteria Definitions**

| Response Category                | Criteria                                                                                                                                                                                                                                                                                                  |
|----------------------------------|-----------------------------------------------------------------------------------------------------------------------------------------------------------------------------------------------------------------------------------------------------------------------------------------------------------|
| Immune Complete Response (iCR)   | All lesions resolved                                                                                                                                                                                                                                                                                      |
| Immune Partial Response (iPR)    | At least a 30% decrease in the sum of the diameters of target lesions, taking as reference the baseline sum diameters.                                                                                                                                                                                    |
| Immune Progressive Disease (iPD) | At least a 20% increase in the sum of the diameters of target lesions, taking as reference the smallest sum on study recorded since the treatment started or the appearance of one or more new lesions. In addition to 20% increase, the sum must also demonstrate an absolute increase of at least 5 mm. |
|                                  | Wait up to 12 weeks to confirm PD to account for flare                                                                                                                                                                                                                                                    |
| Immune Stable Disease (iSD)      | Does not meet other criteria                                                                                                                                                                                                                                                                              |

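### After first RECIST v1.1 progression, the protocol is inconsistent on who approves continued treatment, when progression must be confirmed, and when scanning stops

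*Protocol*

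**What the plan says.** **Approval.** Section 7.3.1 permits treatment beyond PD as per iRECIST if the Investigator sees continuing benefit and judges that "the potential benefit of continuing study treatment outweighs any potential risk, and only with Sponsor approval". It does not say whether first or confirmed PD is meant. Section 7.3.4 opens with "A patient will be discontinued from study treatment (EOT) and/or the study (EOS) for any of the following reasons" and puts PD first in the list, with no exception stated there. Appendix 12.4 says that once RECIST v1.1 PD is identified, "a patient may continue treatment if clinically stable, at the discretion of the Investigator". Only for PD that has been confirmed does it tell the site to contact the Sponsor and to "document the Sponsor approval to continue to treat beyond confirmed PD per protocol".

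**Confirmation window.** The text of Appendix 12.4 reads "Obtain repeat imaging 4 to 8 weeks later to confirm PD". Table 27, in the same appendix, reads "Wait up to 12 weeks to confirm PD to account for flare".

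**End of scanning.** Section 7.4.15 continues tumor measurements "until PD, withdrawal of consent, death, or study termination, whichever occurs first". Footnote u of Table 7 (q3w) and of Table 14 (q1w) uses the same stopping rule. Appendix 12.4 nevertheless calls for repeat imaging after first PD and for iRECIST response data at every visit after it.

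**Use of the data.** Section 2.2.2 makes ORR, DOR and PFS by both RECIST v1.1 and iRECIST secondary endpoints. Section 9.10 uses RECIST v1.1 for the primary response evaluation and iRECIST to capture pseudoprogression, noting that PD must be confirmed for this.

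**The concern.** The interval between first and confirmed PD is the only place where iRECIST can depart from RECIST v1.1. In that interval three operational questions must have one answer each: who allows further dosing, by when the confirming scan is due, and whether scanning goes on. The protocol gives two answers to each, depending on the section read.

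Two things are at stake. One is exposure after first PD in a first-in-human study, and who authorises it. The other is whether the secondary iRECIST endpoints carry information beyond RECIST v1.1. No later analysis rule can recover a scan that was not taken or settle an approval that was not sought.

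**Working it through.** The plan states no figure to reproduce. The check compares the passages and adds supporting arithmetic.

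**1. Approval.**

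| Situation | Section 7.3.1 | Appendix 12.4 |
|---|---|---|
| First RECIST v1.1 PD, not yet confirmed | Sponsor approval, if PD means first PD | Investigator alone, if clinically stable |
| Confirmed PD | Sponsor approval | Sponsor approval |

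The two agree on the first row only if PD in Section 7.3.1 means confirmed PD. The protocol does not say so. It has separate terms for unconfirmed (iUPD) and confirmed (iCPD) progression in its abbreviation list, and Appendices 12.3 and 12.4 attach plain PD to the RECIST v1.1 definition.

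**2. Routine scan dates.** Inputs: scans within 7 days before Cycles 3, 5 and 8, then every third cycle (Section 7.4.15); cycle length 21 days (Section 5.2.1). Nominal scan week = (cycle − 1) × 21 / 7.

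| Scan before cycle | 3 | 5 | 8 | 11 | 14 |
|---|---|---|---|---|---|
| Nominal week | 6 | 12 | 21 | 30 | 39 |

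The gap from the Cycle 3 scan to the Cycle 5 scan is 12 − 6 = 6 weeks (5 to 7 with the 7-day window), which lies inside both confirmation windows. Every later gap is 9 weeks (21 − 12, 30 − 21, 39 − 30), or 8 to 10 with the window. For a first PD seen at the Cycle 5 scan or later, the next routine scan is therefore nominally too late for the 8-week limit but inside the 12-week limit. Which sentence applies decides whether an additional scan is needed.

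**3. Exposure before confirmation.** Assumptions: the first-PD scan falls 0 to 7 days before an infusion, dosing continues on schedule, and infusions before the day of the confirming scan are counted. With offset s from 0 to 7 days, interval i (21 or 7 days) and confirmation at day D, count the k ≥ 0 with s + k·i < D.

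| Confirmation at | q3w infusions | q1w infusions |
|---|---|---|
| 4 weeks (D = 28) | 1–2 | 3–4 |
| 8 weeks (D = 56) | 3 | 7–8 |
| 12 weeks (D = 84) | 4 | 11–12 |

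Moving from 8 to 12 weeks adds 4 − 3 = 1 infusion on q3w and 11 − 7 = 12 − 8 = 4 on q1w.

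**4. What stopping at first PD would do.** Under the dating rules at the end of Appendix 12.4, an unconfirmed progression is ignored only if a later iSD, iPR or iCR is seen. Otherwise its date stands. With no scan after first PD, no later iSD, iPR or iCR can be observed, so the iRECIST progression date equals the RECIST v1.1 date and no response after PD can be recorded. At a site working this way, iRECIST ORR, DOR and PFS repeat RECIST v1.1.

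**The case against.** The strongest counter-argument concerns scanning. Section 7.4.15 itself requires evaluation by iRECIST and points to Appendix 12.4, which requires the repeat scan and provides an eCRF for treatment beyond radiographic progression. Read together, the stop at PD is loose wording for the routine schedule and does not cancel the specific rule. This stands against a stronger inference that a reader might draw: that iRECIST must coincide with RECIST v1.1 by design, that no patient can differ, or that the iRECIST endpoints cannot be measured. Those statements hold only if Appendix 12.4 is ignored. Even then, iRECIST PFS still has a value through the fallback date.

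On approval, Section 7.3.1 speaks of continuing benefit in terms close to the confirmed-PD sentence of Appendix 12.4, so it may have been meant for confirmed PD. A site that always sought Sponsor approval would satisfy both. On the window, a scan at 4 to 8 weeks also meets an outer limit of 12. Both points show that a cautious site can comply with everything. Neither tells a site what is required: the intended meaning of PD is not stated, and a confirming scan at week 10 meets Table 27 but not the text.

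It would also go too far to claim that sites will in fact use different windows, or that two extra q3w infusions are typical. The documents do not show the first, and under the stated counting rule the second is one.

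**Conclusion.** The inconsistencies are in the current text and should be corrected. The 4-to-8-week and 12-week limits differ whatever PD is taken to mean. The approval and scanning conflicts depend on reading unqualified PD as RECIST v1.1 PD, which is how the protocol defines the term and which no section overrides.

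The size is moderate. Between the two window limits the difference is about 1 q3w or 4 q1w infusions per patient kept on treatment. Loss of separate iRECIST information is conditional on a site following the schedule text alone. The number of patients affected cannot be derived from the protocol.

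A reader might infer a threat to dose finding. The documents do not support that: DLT evaluation, the BLRM and determination of the MTD or RDE do not use these rules, and RECIST v1.1 remains the primary response evaluation.

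**What to change.** - Reconcile Sections 7.3.1 and 7.3.4 with Appendix 12.4 on who approves treatment between first and confirmed PD, naming the type of PD each time. The rule is the sponsor's choice.
- Reconcile the text of Appendix 12.4 and Table 27 to one confirmation window, again the sponsor's choice, and say whether a routine scan may serve as the confirming scan.
- In Section 7.4.15 and footnote u of Tables 7 and 14, state which PD ends scanning. Patients treated beyond RECIST v1.1 PD should continue tumor assessments for as long as Appendix 12.4 requires iRECIST data. Ending scans at iCPD would leave a new gap, because Appendix 12.4 allows approved treatment beyond confirmed PD and still asks for iRECIST entries.

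The cost is protocol wording. The confirming scan is already required by Appendix 12.4. Any extra scan after the Cycle 5 assessment depends on the window chosen.
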